## Abstract

**Background:**

Body image concerns are prevalent among Brazilian adolescents and can lead to poor psychological and physical health. Yet, there is a scarcity of culturally-appropriate, evidence-based interventions that have been evaluated and made widely available. Chatbot technology (i.e., software that mimics written or spoken human speech) offers an innovative method to increase the scalability of mental health interventions for adolescents. The present protocol outlines the co-creation and evaluation of a body image chatbot for Brazilian adolescents via a partnership between academics, industry organisations and the United Nations Children’s Fund (UNICEF).

**Methods:**

A two-armed fully remote randomised controlled trial will evaluate the chatbot’s effectiveness at improving body image and well-being. Adolescent girls and boys (*N* = 2800) aged 13–18 years recruited online will be randomly allocated (1:1) into either: 1) a body image chatbot or 2) an assessment-only control condition. Adolescents will engage with the chatbot over a 72-hour period on *Facebook Messenger*. Primary outcomes will assess the immediate and short-term impact of the chatbot on state- and trait-based body image, respectively. Secondary outcomes will include state- and trait-based affect, trait self-efficacy and treatment adherence.

**Discussion:**

This research is the first to develop an evidence-informed body image chatbot for Brazilian adolescents, with the proposed efficacy trial aiming to provide support for accessible, scalable and cost-effective interventions that address disparities in body image prevalence and readily available resources.

**Trial registration number:**

NCT04825184, registered 30th March 2021.

**Supplementary Information:**

The online version contains supplementary material available at 10.1186/s12889-021-12129-1.

## Background

Despite being an emerging global public mental health issue [1] body image research has largely been confined to high-income, White, English speaking populations [2, 3]. Yet, research from Asia, Africa, and South America highlights cross-cultural similarities in the expression of body image concerns. A study in 26 countries found global normative discontent, with most individuals reporting appearance dissatisfaction [4]. Understanding cross-cultural similarities, as well differences allows for the development of new and/or adaptation of extant evidence-based body image interventions for use in traditionally underserved populations. However, interventions must also be accessible, scalable and cost-effective if they are to achieve impact [5, 6]. Multi-stakeholder partnership is a key mechanism for achieving this. This paper outlines the study protocol for the co-creation and evaluation of a scalable body image chatbot (i.e., software that mimics written or spoken human speech) designed with and for Brazilian adolescents through a partnership between academics, industry organisations (beauty [Dove]; communication and technology [Talk2U]) and the United Nations Children’s Fund (UNICEF).

### Body image in Brazil

With a population of over 212 million people ([7]), body image concerns in Brazil are common across the lifespan, particularly among adolescents. Prevalence of body image concerns range between 26.6–56% and 10.7–36% for adolescent girls and boys, respectively [8–10]. Concurrently, up to 10% of adolescents report engaging in disordered eating and unhealthy weight control behaviours [11, 12]. Further, consumer trends show Brazil is the leading country in diet pill consumption and cosmetic surgery, with 2.5 million surgical and non-surgical aesthetic procedures conducted annually [13]. This is concerning given that body image is a key risk factor for depressive symptoms, smoking, substance misuse and self-harm in other countries [14]. Further, cosmetic procedures incur significant financial expense and have potential medical complications [15]. Together, these findings highlight the urgency for easily-accessible, scalable, and cost-effective interventions designed to address body image concerns among Brazilian populations. At present, such interventions are limited.

Existing body image interventions in Brazil have evolved from international collaborations between Brazilian and US researchers. These include the translation and adaptation of a group-based cognitive dissonance intervention, *The Body Project*, which provides a forum for girls and women to challenge unrealistic appearance ideals and develop body satisfaction. The program proved effective at improving body image, negative affect and resilience to sociocultural pressures, but not disordered eating, among at risk Brazilian adolescent girls [16]. *New Moves*, a US program, was also adapted for use with Brazilian adolescents [17]. This school-based program used a combination of motivational interviewing and exercise and nutrition sessions to improve body dissatisfaction, self-esteem and healthy eating behaviours. Despite its efficacy in improving these outcomes among US girls, it did not lead to significant improvements in these key outcomes among Brazilian girls.

To our knowledge, no evidence-based body image intervention has been developed specifically with and for Brazilian adolescents, nor has a research group utilised technology and multi-disciplinary partnerships to develop, evaluate, disseminate and implement an intervention in Brazil. First, given that 24.3 million young people aged 9–17 years in Brazil (86% of the age range) use the internet [18], digital interventions are likely to be accepted by young people, as well as highly amenable to their lifestyles, which are increasingly digitally oriented. Second, the diverse knowledge and expertise held by the partnership stakeholders ensures that relevant insider knowledge from the respective markets are integrated into the intervention development, evaluation, implementation and dissemination frameworks; thus, making for an innovative and well-considered intervention.

### Digital innovation in body image interventions

The emergence of digital interventions has increased the accessibility, scalability, and cost-effectiveness of mental health interventions [5, 6, 19]. A review into the adaptation of face-to-face body image and eating disorder prevention interventions (e.g., psychoeducation, media literacy and cognitive dissonance) for online use show promising results. However, effects are small and significant issues with attrition and adherence are noted (Cohen’s ds .24–.42) [20, 21]. Consistent with recommendations for using disruptive innovation (e.g., ‘edutainment’; educational content within entertainment settings) and technology to scale up mental health interventions [22], researchers have begun developing and testing purpose-built digital body image interventions. Many of these interventions have been designed to be brief, standalone approaches that provide immediate (‘in-the-moment’) symptom reprieve; an intervention model referred to as ‘micro-interventions’ (e.g., audio and visual clips, online games and e-books) [23]. An advantage of micro-interventions is the ability to embed theoretically driven, evidence-based therapeutic techniques into existing digital platforms and social media networks already frequented by adolescents; thus, potentially removing barriers to dissemination and uptake [5, 6, 22].

Micro-interventions are a promising strategy for addressing mental health among Brazilian adolescents, particularly due to the high percentage of young people with internet access (86%) and a social media network (68% [18];). Recently, micro-interventions have proven effective at producing immediate and short-term body image and mental health benefits among adolescents and young adults in Australia [23], the UK [24] and the US [25]. Until now, chatbot technology has not been developed or evaluated within a micro-intervention framework [26], nor has an evidence-based micro-intervention been purpose-built for Brazilian populations. However, a recent public health initiative by UNICEF Brazil [27], reported high uptake and acceptability of a chatbot addressing sexting among adolescents, with over one million users in the first 12-months of dissemination.

Chatbot technology is a robust, low-barrier alternative to traditional mental health approaches, which are largely dependent on health professionals and services for effective implementation and dissemination [5, 6]. Chatbots are usually hosted on a website or app, with the centralised platform allowing users to engage with a variety of intervention techniques, monitor their symptoms and progress, and at times refer at-risk individuals to more appropriate mental health resources and services [26]. This independence from traditional health care approaches also allows for around the clock access and care, particularly to those who have limited mobility, live distant from health professionals and services, or are reluctant to seek mental health advice due to stigmatization [26]. Therefore, given the prevalence of body image concerns among adolescents, coupled with the scarcity of extant prevention and interventions approaches, as well as adolescent’s frequent online behaviours, chatbot technology offers a new and innovative approach to addressing these concerns at-scale.

### The current trial design

This paper outlines the protocol for the co-creation and controlled evaluation of a chatbot targeting risk and protective factors for body image concerns among Brazilian adolescents. A two-arm fully remote randomised controlled trial (Fig. 1) will compare a chatbot intervention to an assessment-only control condition. Participants in the intervention condition will interact with the chatbot over a 72-h period, while participants in the control condition will receive ‘standard care’ for body image concerns among adolescents in Brazil, which at present is no intervention. This protocol paper and the randomised controlled trial design were guided by the Standard Protocol Items: Recommendations for Interventional Trials (SPIRIT; see Fig. 2 and supplementary materials) and the Consolidated Standards of Reporting Trials (CONSORT [28];), including the extension for Electronic Health (CONSORT - EHEALTH [29] see supplementary guidelines).

**Fig. 1 Fig1:**
[figure not shown]
The research design according to the CONSORT EHealth guidelines

**Fig. 2 Fig2:**
[figure not shown]
Schedule of enrolment, interventions, and assessments according to the SPIRIT guidelines

Assessment of primary and secondary trait outcomes will be conducted at baseline (T1), post-intervention (i.e., 3 days; T2), one-week (T3) and one-month follow-up (T4). Participants in the intervention condition will also be assessed on state-based body satisfaction and affect immediately after engaging with each technique. To our knowledge, this is the first chatbot to target body image among Brazilian adolescents. Therefore, a secondary aim is to assess users’ engagement and adherence. Hypotheses were formulated for overall chatbot efficacy (H1-H2), moderation effects within sub-samples (H3), and intervention engagement and adherence (H4):
**H1:** The chatbot was designed to provide immediate benefits to users. Therefore, it is anticipated that adolescents will experience improvements in state-based body satisfaction and affect at the time of engagement with the chatbot.**H2**: Adolescents randomised into the intervention condition will experience greater improvements in trait-based body esteem, affect and body image self-efficacy at post-intervention, one-week and one-month follow-up, relative to the assessment only control condition.**H3:** Based on previous research into the moderating effects of gender [30] and trait psychopathology [31, 32] on body image intervention effectiveness, it was hypothesized that intervention effects will be moderated by gender, and baseline levels of body esteem, affect and body image self-efficacy. Specifically, intervention effects will be greatest among: girls; girls and boys with lower levels of trait body esteem; girls and boys with higher levels of trait negative affect and body image self-efficacy.**H4**: With regards to user engagement and adherence, given the novelty of this intervention, analyses will be of an exploratory nature. It is, however, anticipated that greater engagement and adherence with the chatbot intervention will lead to greater improvements in trait-based outcomes.

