### Measures

Research measures are presented in Table 3. One measure was purpose-built for the current research (i.e., body image self-efficacy). Acceptability and adherence measures were informed by existing reviews [52, 53], with remaining measures validated for use among adolescents.

**Table 3 Tab3:** Research outcomes and internal consistencies

*Demographics*	Age, gender identity, ethnicity, race, state and region of residence	T1
*Primary outcomes*		
State body satisfaction	A single 11-point scale assessing the immediate impact of a chatbot technique on participants’ state body satisfaction (*How satisfied are you with your appearance, right now, in this moment?*). Total score range 0 (*not at all*) to 10 (*very much*). Higher scores reflect greater satisfaction.	Start of chatbot experience. Post-intervention technique. 12-, 16-, 23.5-h after non-engagement.
Trait body satisfaction	Body Esteem Scale for Adolescents & Adults in Brazil [46, 47]. Appearance Positive (AP; e.g., *I like how I look like in photos*), Appearance Negative (AN; e.g., *I feel ashamed about my appearance*) and Weight (e.g., *I am satisfied with my weight*). Mean subscale scores range between 0 (*never*) and 5 (*always*). Higher scores reflect higher esteem. Internal consistency: AP = .85; AN = .88; Weight = .89.	T1- T4
*Secondary outcomes*		
State affect	A single 11-point scale assessing the immediate impact of a chatbot technique on participants’ state affect (*How happy are you, right now, in this moment?*). Total score range between 0 (*not at all*) to 10 (*very much*). Higher scores reflect greater positive affect.	Start of chatbot experience. Post intervention technique. 12-, 16-, 23.5-h after non-engagement.
Trait affect	The Positive and Negative Affect Scale for Children 8-item; PANAS-C8 [48] 8-items related to emotive states (4 positive [e.g., *joyful*]; 4 negative [e.g., *irritated*]). Positive and negative affect subscale scores range between 1 (*not at all*) and 5 (*extremely*). Higher scores reflect greater positive or negative affect. Internal consistency: PA = .77; NA = .76	T1 - T4

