### Statistical power

The limited number of prior micro-interventions and insufficient detail for key parameters complicates efforts to confidently generate all required parameter estimates for power calculations. Accordingly, we adopted a Monte Carlo simulation approach that tested power across a range of combinations of key statistical parameters for multilevel modelling: within-person sample size (varying from 3 to 5 estimates per person), intraclass correlation (ICC) for outcome (ranging from .3 to .6 in recognition that ICC values tend to be large for repeated measures designs), random slope variance (choosing .01, .09, and .25 to reflect small, moderate, and large amounts of variance [54]), and effect size (setting at *r* = .2 to reflect small yet practically meaningful effect size [55]).

Using the SIMR (simulation-based power calculations for mixed models) package in R [56], we tested power across these different combinations of parameter estimates, with power set at .80, alpha = .05 (two-tailed), equal allocation to intervention and control arms, and conservatively allowing for 25% attrition on an initial sample of 2800 participants at the final timepoint. We note too that Hypotheses 1 and 4 are limited to the intervention arm, and thus the sample size used for those calculations was 1050 (1400 participants with 25% attrition). Using these inputs, our simulations indicated power was > .99 for all cross-level interaction effects regardless of input values, and > .80 for all within-person effects with the exception of scenarios where: (1) the random slope variance was small, or (2) a small-to-moderate random slope variance was accompanied by a small number of within-person estimates (average cluster size of 3–4). These scenarios of small random variance coupled with a small estimated effect size are unlikely based on best available evidence from past studies [23–25]. Thus, our sample size is likely to be sufficient across a range of plausible data scenarios.

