### Data analyses

At trial completion, Toluna and Talk2U will deliver password protected datafiles to the corresponding author who will clean, screen and separate state- and trait-based data for blinding purposes. Data will then be delivered to the data analysts. Analyses will be conducted in Stata. A series of linear mixed effects models will test hypotheses. H1 analyses will be limited to intervention arm participants as there is no comparable pre- and post-technique data for the assessment-only arm, while analyses for H2, H3 and H4 will include participants from both study arms.

To test H1, the immediate effects of intervention content on state-based outcomes will be explored by regressing state-based outcome measures (body satisfaction and affect) onto a time variable (0 = pre-content, 1 = post-content). For H2-H4, scores on trait-level outcome variables will be regressed onto a dummy coded time variable, with baseline as the reference category compared against post-intervention, one-week, and one-month follow-up timepoints, using random effects to allow for individual differences in amount of change in symptoms over time. Group (control = 0, intervention = 1) will be included as a cross-level moderator to test group differences in change over time (H2). The moderating effect of baseline variables on this group effect will be conducted to test H3. In evaluating H4, adherence and engagement measures will be tested as moderators of change in trait-based outcome measures over time (relative to baseline) for intervention participants. Relations among random effects of Level 1 time variables will be modelled with an unstructured covariance matrix.

Baseline differences between intervention and control participants in terms of demographic factors will be tested. Any variables shown to differ across groups will be included as covariates in analyses. Linear mixed model results will be presented in adjusted and unadjusted forms to demonstrate impact of these covariates on results.

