### Dissemination

Research findings will be disseminated via open-access peer reviewed publications and academic conferences, as well as beyond the scientific community. Findings will be shared through infographics and videos to interested members of the public, including on the social media platforms and websites of the Dove Self-Esteem Program, UNICEF and Talk2U. If the intervention proves effective, the chatbot will be scaled up for delivery to adolescents across Brazil via social media marketing campaigns targeting audiences directly on *Facebook*, *Instagram* and *TikTok*.

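### Ten candidate primary tests, with no primary subscale, visit or success rule: the false-positive rate behind 'effective' depends on a reading that the protocol leaves open

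*Protocol article*

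**What the plan says.** The Abstract (Methods) sets two primary constructs: "Primary outcomes will assess the immediate and short-term impact of the chatbot on state- and trait-based body image, respectively". Table 3 (Measures) lists both as primary. State body satisfaction is a single item. Trait body satisfaction is the Body Esteem Scale with Appearance Positive, Appearance Negative and Weight, scored by subscale ("Mean subscale scores range between 0 (*never*) and 5 (*always") with no total described.

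H2 (The current trial design) predicts "greater improvements in trait-based body esteem, affect and body image self-efficacy at post-intervention, one-week and one-month follow-up, relative to the assessment only control condition". That sentence mixes the primary trait outcome with secondary ones (affect, self-efficacy), so the primary family has to be read from the Abstract, Table 3 and Data analyses together.

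Data analyses fits a mixed model for each trait score with dummy-coded time, "with baseline as the reference category compared against post-intervention, one-week, and one-month follow-up timepoints", and treatment group as cross-level moderator. It does not say whether the three visit contrasts are tested singly or jointly. For the state outcome, "H1 analyses will be limited to intervention arm participants as there is no comparable pre- and post-technique data for the assessment-only arm".

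The only significance level is in Statistical power: "with power set at .80, alpha = .05 (two-tailed", an input to the simulation. Dissemination states the consequence: "If the intervention proves effective, the chatbot will be scaled up for delivery to adolescents across Brazil". The Discussion likewise makes public release conditional on efficacy. Neither section says which contrast, or how many, must be positive.

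**The concern.** A protocol that names its primary outcomes, gives their scoring and fixes the model should also make clear which comparison decides the trial. Here a positive result on Weight at one week only, or on the state item only, could be presented as meeting the primary objective; so could a requirement for consistent benefit across visits. These readings carry very different false-positive risks, and the choice between them could be made after the results are known. What rests on it is a decision to offer the chatbot to adolescents across Brazil.

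The state test raises a separate difficulty. It is a pre-to-post comparison within the intervention arm, restricted to instances with both ratings. A positive result can arise without any causal effect of the chatbot, so a 5% level does not bound the risk of a false efficacy claim from that test.

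**Working it through.** **Inputs.** From the protocol: 1 state outcome; 3 trait subscales; 3 post-baseline visits; two-sided alpha .05; 2800 randomised 1:1; 25% attrition; r = .2; ICC .3 to .6; random slope variance .01 to .25. Assumed, because not given: correlation between the test statistics of different subscales (0 to .8) and of different visits (0 to .8; change scores sharing a baseline correlate .5 under compound symmetry), with the state test independent of the trait tests.

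**The plan's own figures.** 1400 × (1 − 0.25) = 1050 per arm, as stated. Converting r to a standardised difference, d = 2r/√(1 − r²) = 0.4/√0.96 = 0.408. Taking the change-score SD as √(2(1 − ICC) + slope variance), power for one group-by-visit contrast at alpha .05 exceeds .99 at ICC .3 and .6 with every stated slope variance. This agrees with the protocol's > .99 for cross-level interactions. It is an analytic check, not a rerun of the simulation.

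**Count.** 3 subscales × 3 visits + 1 state test = 10.

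**Family-wise error if any one of ten separate tests at two-sided .05 counted.**
- Independent: 1 − .95¹⁰ = .401. Trait tests alone: 1 − .95⁹ = .370.
- Correlated (400,000 simulated draws, nine trait statistics plus one state statistic):

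| Subscale corr. | Visit corr. | Any rejection | Rejection in the chatbot's favour |
|---|---|---|---|
| 0 | 0 | .40 | .22 |
| .3 | .5 | .35 | .18 |
| .5 | .5 | .33 | .17 |
| .5 | .7 | .30 | .15 |
| .7 | .7 | .26 | .14 |
| .8 | .8 | .225 | .115 |

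The favourable-direction figure for independent tests is 1 − .975¹⁰ = .224. Its single-test benchmark is .025, not .05.

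**Other readings of the same text.**
- One joint 3-df group-by-time test per subscale plus the state test: 1 − .95⁴ = .185 if independent; .16 to .18 at subscale correlations .3–.7 and visit correlations .5–.7.
- A subscale must show benefit at all three visits: .004 to .013 over the same correlations, trait outcomes only.

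**Cost of controlling the trait family.**
- Effect detectable with 80% power, in SD units of the analysed change, 1050 per arm: (1.960 + 0.842) × √(2/1050) = 0.12 at .05, and (2.394 + 0.842) × √(2/1050) = 0.14 at .05/3. Ratio 3.236/2.802 = 1.155.
- At Holm's first step over nine, .05/9: (2.773 + 0.842)/2.802 = 1.29, or 0.16 SD.
- Power at d = 0.408 and alpha .005 (stricter than .05/9), with the largest change-score SD considered, √(2 × 0.7 + 0.25) = √1.65: above .99.

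**The case against.** **The protocol never says that one significant test suffices.** This is right, and it limits the claim. A reader might infer a 25–40% chance of a false primary success. The documents do not support that as a statement of fact. Alpha .05 appears only in the power section; the visit contrasts could be tested jointly; and the 'and' joining the three visits in H2 can be read as requiring benefit at each. The two-sided figure also counts results in which the chatbot does worse, and those would not lead to roll-out. In the chatbot's favour the range is about half as large. What stands is that the text allows all of these readings and chooses none.

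**This is a journal article, and multiplicity rules usually sit in the analysis plan.** Also right, so the absence of an adjustment method is not the point here. The point is that the article defines its primary outcomes and its model in a way that leaves the deciding contrast open.

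**Trait analysts are blinded to condition.** This limits picking a subscale or visit by the direction of its effect. It does not define success, and it does not cover the state outcome, whose analysis the protocol says cannot be blind.

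**Moderation tests.** A reader might add the H3 interactions to the tally. They should stay out. The protocol assigns overall efficacy to H1 and H2 and does not say that every moderator is crossed with every outcome and visit.

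**Conclusion.** The point holds as one of definition. As written, the plan yields ten candidate primary tests, nine randomised and one uncontrolled, with no primary subscale, visit or success rule behind the word 'effective'. The false-positive rate is therefore not fixed. It is about 25–40% (22.5% at correlations of .8) if any two-sided rejection counted, about 12–22% in the chatbot's favour, about 16–18.5% with joint tests per subscale plus the state test, and about 0.4–1.3% if a subscale had to show benefit at all three visits.

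These figures assume the correlations shown, an independent state test and no true effect anywhere. They describe the multiplicity only and do not capture the bias of the uncontrolled state comparison. The point does not question the design or the sample size, and settling it needs only a change of wording.

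**What to change.** Define the confirmatory family as the nine randomised body-esteem contrasts (three subscales at T2, T3 and T4) and control it at two-sided .05 in one of two ways:

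1. Holm over all nine contrasts; or
2. allot .05/3 to each subscale and test its three visits in a pre-stated order, each at that same .05/3, stopping at the first non-rejection.

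The level must not revert to .05 for later visits. For example, suppose Holm is applied across subscales at T2 only and T3 is then tested at .05. If one subscale truly works at T2 only and the other two are null, the error is about 1 − .95 × .975² = 9.7% with independent tests.

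State that 'effective', in Dissemination and the Discussion, means at least one rejection in this family in the chatbot's favour. State body satisfaction can keep its place as a measure of immediate response, but the within-arm result alone should not establish efficacy. The visit order under option 2 is for the investigators to choose; the protocol gives no basis for preferring one.

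**Cost.** Wording, plus a somewhat larger detectable effect: about 15% at .05/3 (0.12 to 0.14 SD) or about 29% at Holm's first step (0.16 SD). At the planned r = .2, read as d = 0.408, power per contrast stays above .99 with 1050 per arm, so no extra participants are needed. If the .2 was instead meant as a difference of 0.2 SD, power at alpha .005 would be about .78 in the least favourable case (ICC .3, slope variance .25), so the text should say which is intended.
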